**Summary of primary variables.**

Phsycometric measures**CACIA**:**Delay of gratification percentile (RR)**: This percentile indicates the ability to postpone immediate rewards for larger, later benefits, a key aspect of impulsivity and self-control. The higher percentile the better self-control in delaying gratification.**Criterial Self-Control Percentile (CSC)** : This percentile reflects a general capacity for self-control in situations requiring judgment and adaptation to specific criteria
**CBCL and YSR****Aggressive behavior T-score**: A continuous variable reflecting the severity of aggressive behaviors reported by parents (CBCL) or the youth themselves (YSR). Scores above 60 or 65 are often considered in the clinical range.**Externalizing problems T-score**: This variable asessess a broader spectrum of outward-directed problem behaviors, including aggression, rule-breaking, and defiance. Higher scores indicate more severe externalizing problems.

Physiological measures**HR**: Measured in bpm, this continuous variable is affected by both PNS and SNS.**HRV (RMSSD)**: A continuous variable that also shows the activity of the ANS. A reduced HRV is associated to a high SNS activity in healthy subjects.**SCL**: This is a continuous variable, measured in microsiemens (μS), that reflects sympathetic activity linked to emotional arousal.

### Analysis

The statistical analysis will be performed in Matlab 2024.

#### Assessment of cognitive therapy with biofeedback.

The main goal of this study is to verify the efficacy of the proposed therapy. At the beginning adolescents will fill in the CACIA, Stroop, WCST and CBCL tests. At the end of the therapy, these metrics will be assessed once more to compute the difference with the initial tests. These differences will be compared between the intervention and control groups to ascertain statistical significance. To this end, we will use the Mann-Whitney-Wilcoxon test, or the one-way ANOVA, depending on the distribution of residuals, to determine whether samples originate from the same distribution

#### Significant physiological features for aggressive outbursts detection.

We will also extend the statistical analysis to gauge how an aggressive outburst influences all physiological signals. To attain this objective, we will collect features from the last minute of relaxation period, in order to build a set to compare with the features associated with the 60-second data segment that contains the aggressive episode. For each participant there will be a maximum of 7 sets of features for any physiological signal, which will be obtained from sessions S2–S4 and S6–S9, considering that the evoking phase is successful. Statistical analysis will be applied to every feature individually. Friedmann’s test or ANOVA, with repeated measures will be applied to assess the difference between measures before and during the outburst. Friedmann’s test is a non-parametric method suitable for analyzing ordinal data or data that do not meet the assumptions of normality and homoscedasticity; it is also specifically designed for repeated measures or matched group data, allowing for comparisons across multiple conditions or time points for the same subjects. ANOVA will be applied for normally distributed data.

The analysis will be applied to each participant individually and for all participants globally. In order to reduce biases among individuals, features obtained during the baseline phase will be removed from the other phases.

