Difficulties in self-regulation (which includes inhibitory control) linked to interoception can contribute to these problems in individuals with borderline personality disorder (BPD) symptoms [12]. Our internal emotional state shapes our perceptions of others. During a stressful interview, the researchers found that participants with lower interoceptive accuracy were more likely to misattribute their own stress responses to negative traits in the interviewers, perceiving them as less helpful or more hostile. In contrast, individuals with higher interoceptive awareness were better able to distinguish their internal stress from external cues, leading to more accurate and unbiased social judgments. These findings highlight the role of interoception as a protective factor in reducing social misperceptions during emotionally charged situations [13].

The amygdala and PFC, along with many other brain regions, are connected to the hypothalamus [14], which regulates the sympathetic and parasympathetic branches of the autonomic nervous system (ANS) that innervate the heart, sweat glands, and other organs. As a result, the activation or deactivation of these areas induces changes in heart rate, blood pressure, skin temperature, respiration rate, and sweating, leading to a certain level of physiological arousal. Consequently, the detection of peripheral activity could help patients identify their emotions. For example, it is known that heart rate is accelerated or reduced by the activity of the SNS and PNS, and, for this reason, it can be associated with emotional dysregulation [15]. Some authors have monitored heart rate and its variability concerning aggressive episodes using off-the-shelf wearables [16]. Elevated heart rates can occur during an outburst, although authors did not find conclusive results due to the population size used (3 participants). Another study has also reported significant differences between diminished HRV in people with IED, depression, and post traumatic stress disorder (PTSD) when compared to healthy volunteers [17]. Similarly, other studies focused on skin sweating, such as that of Tonacci *et al*. [18] observed higher levels of sympathetic arousal in SCL for anger and sadness stimuli in children with aggression problems, and Deutsch *et al*. [19] detected an increase in skin conductance in subjects with outbursts of combative behavior.

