**Block 2.**

The second block consists of a recording session at the laboratory, which is repeated three times.

S2–S4 In these sessions, parents, scientists, adolescents and psychologists will meet to try and reproduce the outburst and record physiological signals before, during and after the aggressive episode.These sessions contain several phases:**Baseline register.** Initially, the researchers will set up the system and start recording a baseline reference for approximately 5 minutes [36].**Relaxation.** After the baseline register phase, adolescents will move on a relaxation phase, in which they will use an immersive Virtual reality (VR) system for 10 minutes. In this phase, participants can move into a landscape while listening to ambient sounds (birds and sea waves). VR, particularly immersive virtual reality (IVR), has demonstrated its effectiveness in therapy with people with behavioral disorders, improving emotion recognition, social skills, and attention, while diminishing their anxiety and phobias [37–39].**Evoking an outburst.** In the following phase, adolescents will watch the recorded aggressive outburst while their parents explain to the therapist the reasons that caused such an episode, including all the necessary details that favor the elicitation of a new outburst. Different videos will be used in each session to avoid the accommodation effect. Re-experiencing a situation that previously triggered an anger outburst can indeed provoke it again. This is because recalling emotionally charged events can activate the same brain areas involved in the original emotional experience [40]. According to the classical conditional model, if a particular situation has been previously associated with an anger response, re-exposure to that situation can trigger anger again due to conditioned memory [41].**Relaxation.** At the end of the episode, parents will leave the room for a while, and the participants will go to a new relaxation phase for another 10-minute period using again the VR.

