Fig 2 depicts the phases and actions in this important session. The experimenter will tag the beginning of each phase in this session and will mark the moment when the impulsive outburst appears. By doing so, researchers will be able to analyze offline how the physiological information changed and how it can be included in the therapy. There will be a digital diary to collect tests outcomes and any relevant information regarding the patient during the session, including whether the outburst was evoked successfully. Data will be discarded from analysis when it is not possible to evoke the outburst.

The data collected in this block will allow assessing the influence of an aggressive episode on physiological signals. This will be used to teach individuals to identify when an outburst is about to occur, and prevent it.

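### The outburst analysis compares VR rest with a provoked outburst, so a significant difference cannot be credited to the outburst itself

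*Protocol article*

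**What the plan says.** All places are in the protocol article.

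- **Aim.** The Analysis subsection on significant physiological features sets out "to gauge how an aggressive outburst influences all physiological signals".
- **Reference.** "we will collect features from the last minute of relaxation period, in order to build a set to compare with the features" of "the 60-second data segment that contains the aggressive episode".
- **Test.** Friedman, or ANOVA "with repeated measures will be applied to assess the difference between measures before and during the outburst". Each participant contributes at most 7 feature sets, from S2–S4 and S6–S9. Baseline-phase features are removed from the other phases.
- **What relaxation is.** Under Block 2, participants enter a phase "in which they will use an immersive Virtual reality (VR) system for 10 minutes", with a landscape and ambient sounds.
- **What surrounds the episode.** Also under Block 2, "adolescents will watch the recorded aggressive outburst while their parents explain to the therapist the reasons that caused such an episode", with the details chosen to help bring on a new outburst. S6–S9 keep this layout apart from the last phase.
- **Onset and failed evocations.** The experimenter marks the moment the outburst appears. "Data will be discarded from analysis when it is not possible to evoke the outburst".

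**The concern.** The stated question is about the outburst. Moving from the relaxation minute to the episode segment changes several things at once: the VR scene ends, the video starts, the parents speak, and the outburst happens. The Introduction gives a reason to expect the stimulus alone to matter for one of the three primary physiological measures: an earlier study "observed higher levels of sympathetic arousal in SCL for anger and sadness stimuli in children with aggression problems".

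The protocol lists identifying the most significant features among its further aims, and its Conclusion wants a small set that best predicts an incoming outburst, to be merged into a warning signal. A feature that separates rest from the evoked state may mark an outburst, or may mark a child who is upset by the video. This contrast cannot tell the two apart. The recordings that could help, those with provocation but no outburst, are discarded.

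**Working it through.** **1. Plan's own count.** S2–S4 gives 3 sessions and S6–S9 gives 4; 3 + 4 = 7, as stated.

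**2. What the contrast estimates.** Within one session let B be the baseline level, R the VR-relaxation level, P the shift from R caused by the evoking situation, and O the shift added by the outburst.

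- Relaxation segment after baseline removal: R − B
- Episode segment after baseline removal: R + P + O − B
- Difference: P + O

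B cancels, so baseline removal does not separate P from O. The null tested is P + O = 0, not O = 0.

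**3. Whether another analysis isolates O.** The home-versus-lab comparison uses data following the labelled episodes in both settings, so it has no provoked, no-outburst reference. Onset is tagged, but no evoking-phase window before onset enters the test. S2–S4 contain two relaxation phases; the before-and-during wording points to the first, and the problem is the same with either.

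**4. Size if O = 0.** Inputs: N = 70 (Participants); alpha 0.05 (stated for the sample size, taken here as two-sided); one averaged pair per participant; provocation effect dz, in SD of the paired difference, assumed at 0.2, 0.3 and 0.5.

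*Repeated-measures ANOVA with two levels (paired t).* The noncentrality is dz × √N and the critical value on 69 df is 1.995. At dz = 0.2, for example, it is 0.2 × √70 = 1.673.

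*Friedman with two conditions.* The statistic is (2k − N)²/N on 1 df, where k is the number of positive differences and each is positive with probability Φ(dz). At N = 70 it rejects when k ≥ 44 or k ≤ 26.

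| N | dz | Noncentrality | ANOVA rejects | Φ(dz) | Friedman rejects |
|---|---|---|---|---|---|
| 70 | 0 | 0 | 5.0% | 0.500 | 4.1% |
| 70 | 0.2 | 1.673 | 37.8% | 0.579 | 23.9% |
| 70 | 0.3 | 2.510 | 69.7% | 0.618 | 48.0% |
| 70 | 0.5 | 4.183 | 98.5% | 0.691 | 89.6% |
| 35 | 0.5 | 2.958 | 82.0% | 0.691 | 61.0% |

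The N = 35 row illustrates evocation succeeding in only half the participants. The dz = 0 row shows that the tests hold their level; the excess comes from P.

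**5. Check of a same-session reference.** A simulation set O = 0, a stimulus effect of 0 to 0.8 within-participant SD, and a between-participant SD of 0.5 in the stimulus response, with 3,000 replicates per setting. Designs were 70 participants × 7 sessions, 70 × 3 and 35 × 3. The planned contrast at a stimulus effect of 0.2 rejected 75.3%, 57.2% and 29.6% of the time (ANOVA) and 52.4%, 37.4% and 18.7% (Friedman). Against a same-session window with the stimulus present and no outburst, rejection was 4.2% to 5.4% (ANOVA) and 3.4% to 4.9% (Friedman) throughout. This supposes that the stimulus effect is the same in both windows.

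**The case against.** The strongest reply is that rest versus outburst is a legitimate contrast. The protocol says the test compares measures before and during the outburst and never claims to separate the outburst from its trigger. In S5 the adolescents are taught to tell their relaxed response from the one that comes with an approaching outburst, and the relaxation contrast suits that purpose. Arousal rising under provocation may even be the early signal the biofeedback needs. This stands: the contrast should be kept, and the problem is what may be concluded from it.

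A second reply is that the rejection rates are ordinary power at an assumed dz, with the outburst effect also assumed to be zero. That stands too. They show how far a significant result could arise without any outburst effect; they do not estimate how often it will.

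A reader might go further and infer that almost every arousal feature will be declared an outburst feature. The documents do not support this. At dz = 0.2 the rates are 24% to 38%, and the cited stimulus finding concerns SCL, not HR, HRV or the wider feature set. Nor does the protocol say that predictors will be chosen by this test alone; its limitations section also mentions training artificial intelligence models.

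A reader might also want sessions without an outburst as the main reference. That would be unsound. Videos differ between sessions. S6–S9 deliver therapy meant to help avoid outbursts, with biofeedback in one arm only. A session without an outburst has no onset to match on.

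**Conclusion.** The point holds as a limit on inference. The planned contrast estimates provocation plus outburst against VR rest, so significance supports a statement about the evoked state versus rest and not one about the outburst. This follows from the design and needs no numerical assumption.

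Its possible size does rest on assumptions. With no outburst effect and dz of 0.2 to 0.5, the test rejects 38% to 98% of the time (ANOVA) or 24% to 90% (Friedman) at N = 70. The documents supply no dz.

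The analysis serves a secondary objective, and the between-arm efficacy comparison is untouched. A change is still worth making, because it is cheap and alters what this analysis can conclude.

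**What to change.** 1. In the subsection on significant physiological features, keep the relaxation contrast but report it as evoked state versus rest.
2. Add there a same-session contrast of the outburst segment with an evoking-phase window ending before the tagged onset, using a mixed model with a participant random effect.
3. Under Block 2, replace the discard rule so that recordings without an outburst are kept as a supportive provoked, no-outburst reference. Adjust for session and arm, and interpret with caution because videos and therapy differ between sessions.

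**Cost.** Protocol and analysis wording and a little more analysis work; the sessions are recorded and the onset tagged already. Some outbursts may start too early to leave a pre-onset window. That window may also already contain preparatory arousal, so the added contrast may understate the outburst effect; the report should say so.

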**Block 3.**

S5 Only for the intervention group. The adolescents will be trained to identify the physiological response when they are relaxed and when an outburst is coming. It is possible to use these responses to predict the aggressive outburst at least one minute before it manifests [42]. To do this end, the VR system receives and shows HR, HRV, and SCL on the virtual scenario. Therapists will help participants identify the physiological features related to aggressive outburst based on the data collected in previous sessions (Block 2).S6–S9 They are similar in both intervention and control groups, and follow the same layout as the sessions in block 2, excluding the last phase:**Cognitive therapy in the control group.** After evoking an outburst, adolescents will be trained with cognitive, behavioral and emotional self-regulation therapies [43], which have proven their effectiveness for managing anger and learning positive coping skills. The underlying theory is that people can minimize their negative feelings and behaviors when they are aware of their irrational beliefs and work to change their minds, by focusing on them continuously. With this therapy, people are endowed with strategies to improve their capabilities of identifying negative thoughts and beliefs in situations of conflict and/or frustration, which are the main triggers of aggressive outbursts. The goal is to ensure that, through identifying such thoughts and becoming more aware of their emotions, the individual gradually dismantles those irrational thoughts.**Cognitive therapy in the intervention group.** Participants will follow the same cognitive therapy as the controls, although they will receive information through biofeedback. By identifying this information and applying the skills learned in therapy, participants are expected to better manage or avoid imminent outbursts.

At the end of session S9, the CACIA, Stroop, CBCL, YSR and WCST tests will be assessed again. The differences between the new obtained physcological scores, with respect to the initial scores, along with the differences between control and intervention groups, will be used to assess the efficacy of the intervention.

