#### Comparison between lab and home scenarios.

Friedman’s test will verify the statistical significance of the SCL and cardiac features between the two scenarios: home and clinic. Firstly, researchers will label the time point in which an aggressive episode takes place in the temporal series. The 60s data after those labels will be segmented using the window lengths and overlaps of 30s and 50% respectively. Features will be obtained for each window and grouped into two sets, which will be used as input to Friedman’s test or to ANOVA with repeated measures.

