## Conclusion

By using biofeedback with cognitive, behavioral and emotional self-regulation therapies, we aim to improve the social skills of people with emotional dysregulation and reduce the frequency of aggressive episodes. This randomized control trial seeks to evaluate the effectiveness of including biofeedback in the therapy.

Although we will use HR, HRV and SCL for biofeedback purposes, a wider set of physiological features will also be studied. The goal is to pinpoint a small and significant set of features that are the best predictors for an incoming outburst.

This reduced set of features could allow designers to develop a minimal piece of equipment. The signals in the ensuing set could then be merged into a unique warning signal before the outburst so that people can apply the learned self-regulation mechanisms, and avoid or minimize the aggressive episodes.

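### The planned physiological contrasts show how an outburst changes the signals, but cannot separate features that precede an outburst from features that only accompany it

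*Protocol article*

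**What the plan says.** **The windows.** The section on significant physiological features in the protocol article gives its purpose as "to gauge how an aggressive outburst influences all physiological signals". For the reference, "we will collect features from the last minute of relaxation period"; these features are set against those from "the 60-second data segment that contains the aggressive episode". A repeated-measures test is then applied to each feature "to assess the difference between measures before and during the outburst". The home-versus-clinic section also starts at the episode: "The 60s data after those labels will be segmented".

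**The use of the results.** Block 2 says that what is learned about the influence of an episode will serve to "teach individuals to identify when an outburst is about to occur, and prevent it". Block 3, on session S5, states from a cited source that the responses can "predict the aggressive outburst at least one minute before it manifests". Study limitations speaks of identifying the preparatory state ahead of an outburst. The Conclusion sets the goal to "pinpoint a small and significant set of features that are the best predictors for an incoming outburst".

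**The data.** Block 2 records signals before, during and after the episode, and the experimenter marks the moment the outburst appears. At home (S1), parents annotate when episodes started.

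**The concern.** A predictor has to change before the event. The stated contrast calls its reference period before the outburst, but that period is the end of a virtual-reality relaxation phase, which finishes before the evoking phase starts. It represents a relaxed state, not an approaching outburst. The other arm of the contrast is taken from the outburst itself. Study limitations also warns that movement during an impulse could disrupt the signals, so this arm is the more exposed to artefact.

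If results from this contrast are reported as predictors, a feature that moves only once the outburst is under way could be put forward as an early warning. A feature that moves beforehand and then returns to its relaxed level could be missed.

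**Working it through.** **1. The plan's own count.** The article gives at most 7 feature sets per participant and signal, from S2–S4 and S6–S9: 3 + 4 = 7. This reproduces. The point rests on no sample-size or power figure in the article.

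**2. The windows side by side.**

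| Analysis or statement | Time relative to onset |
|---|---|
| Feature analysis, reference | last minute of relaxation, before the evoking phase |
| Feature analysis, comparison | 60 s containing the episode; position of onset not fixed |
| Home versus clinic | 60 s after the label |
| Block 2 use, Conclusion goal | before onset |

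No row that is tested is a separate pre-onset window.

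**3. Could the segment containing the episode supply one?** If onset falls *o* seconds into the segment, it holds *o* s before and 60 − *o* s after onset. With onset at the start, that is 0 s and 60 s; with onset in the middle, 30 s and 30 s. For a feature that averages over the window, a shift δ present only before onset moves the segment mean by δ·*o*/60, and one present only after onset by δ·(60 − *o*)/60. At *o* = 30 and δ = 0.5 SD both equal 0.25 SD, so the two kinds of feature look the same. Seconds before onset, if included, are pooled with outburst data and give no separate test.

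**4. Illustration.** The assumptions below are not from the article, apart from the planned sample size: 70 participants, one pair each, independent normal noise with SD 1, shift 0.5 SD, paired t-test, two-sided α = 0.05, segment starting at onset. Rejection rates from 2,000 simulated trials:

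| Feature changes | Relaxation vs outburst (planned) | Relaxation vs minute before onset |
|---|---|---|
| only during | 0.83 | 0.06 |
| before and during | 0.83 | 0.84 |
| only before | 0.06 | 0.82 |

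Check by normal approximation: the paired difference has SD √2, so power ≈ Φ(δ√(70/2) − 1.96). For δ = 0.5 this is Φ(2.96 − 1.96) = Φ(1.00) ≈ 0.84, in line with the simulation.

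Range: δ = 0.2 gives Φ(1.18 − 1.96) ≈ 0.22; δ = 0.8 gives Φ(4.73 − 1.96) > 0.99. The size of the shift alters every rate, but the first two rows of the planned column stay equal, because that contrast depends only on the shift during the outburst.

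**The case against.** **The contrast fits its own stated aim.** The Introduction lists as a further aim how aggressive episodes influence the signals, and the analysis section repeats it. Relaxation versus outburst answers that. This stands, and it is why the planned contrast should be kept. The mismatch is with the use in Block 2 and the goal in the Conclusion.

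**The biofeedback does not depend on this test.** A reader might infer that the intervention cannot be delivered without it. The article does not support that. HR, HRV and SCL are chosen in advance, therapists in S5 work from each participant's Block 2 data, and the test pools sessions up to S9, so it is complete only after therapy has been given. The one-minute lead time rests on a cited source.

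**No selection procedure is described.** A reader might also infer that features will be ranked on this contrast and built into a warning signal. The article tests each feature individually and presents the warning signal as a future possibility.

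**Pre-onset data may be used elsewhere.** The article mentions offline analysis and the training of artificial intelligence models without detail, and an article condenses a fuller protocol. So it cannot be said that pre-onset data go unused. It can be said that neither of the two physiological analyses it does specify isolates them.

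**A simple pre-onset contrast has its own weakness.** In the lab, the minute before onset falls within the evoking phase, while the participant watches the video and the parents explain the episode. Comparing it with relaxation alone would also pick up the change of task. This stands and shapes the fix.

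**Conclusion.** The point holds for the exploratory physiological aim. As specified, the two analyses identify features that accompany an outburst. They cannot tell these from features that precede it, so they do not support the Conclusion's goal of finding predictors or Block 2's use for recognising an approaching outburst. This follows from where the windows lie and does not depend on an effect size; the rejection rates only illustrate it under the assumptions given. It also rests on reading the relaxation period as the one before the evoking phase, which the before-and-during wording implies.

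The reach is limited. The main efficacy comparison, of change in psychological test scores between groups, does not use these windows and is unaffected, as is delivery of biofeedback. It is worth settling before analysis, so that markers of the outburst are not reported as its predictors.

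**What to change.** - Keep the planned contrast, labelled as the analysis of signals during the outburst.
- For the predictor aim, add a separate window of 60 s ending at the tagged onset, with no post-onset data.
- In the lab, compare that window with the last minute of relaxation and, where the time before onset allows, with an earlier part of the same evoking phase, so that reaction to the change of task is not read as a precursor. Sessions in which no outburst was evoked, which Block 2 now discards, could be kept for this analysis as a further reference.
- For home recordings, use an earlier quiet segment as the reference, because S1 has no relaxation phase.
- Base any statement about predictors on the pre-onset contrast only. If it is not added, limit the wording in Block 2 and the Conclusion to concurrent markers.

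A window ending at onset speaks to the final minute only; it would not by itself confirm a lead time of a minute or more.

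**Cost.** No new measurements are needed, because signals are already recorded before onset and the outburst is already marked. There is a little more analysis work, and sessions without an outburst would have to be retained. Pre-onset segments will be short or missing when an outburst starts soon after the evoking phase begins, and the number lost this way should be reported.
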